### Interventions

2.4

The memorization intervention consists of structured recitation of Chinese Classics for a minimum of 5 min per day. The selection of Chinese Classics will be determined collaboratively by the research team and participants. Various memorization strategies will be introduced, including intensive repetition techniques and visualization strategies. Participants may begin by reading the designated text aloud for at least 5 min daily before progressing to full memorization. The research team recommends beginning with the classical text “Di Zi Gui,” translated as Standards for Being a Good Student. To facilitate adherence and standardization, a mobile application currently under development will assist participants in memorization training, provide access to digital literature materials, and record daily recitation duration.

After six consecutive months of training, participants in the intervention group will undergo a standardized recitation assessment. The primary performance metric will be the number of correctly recited Chinese characters within a fixed time frame. For example, Di Zi Gui contains 1,080 Chinese characters. Participants will be required to recite the entire text within 11 min, with no more than eight omitted or incorrectly recited characters. Participants who meet these criteria will be classified as having passed the assessment. The recitation assessment will be conducted by qualified judges affiliated with the Bliss & Wisdom Foundation of Culture and Education, who are capable of reciting the complete text from memory. During evaluation, judges will reference the original text while participants perform their recitation to ensure objective scoring accuracy.

### Outcome measurement

2.5

As described in the Sample Size section, functional MRI serves as an exploratory mechanistic outcome measure, detecting changes in task-related brain activation. The unit of measurement will be the percentage change in whole-brain blood-oxygen-level-dependent signal (%). APOE genotyping will be offered as an optional ancillary component of the study and used for exploratory analyses to investigate potential associations between genetic risk and intervention outcomes.

All other outcomes are defined as secondary outcomes, including:

changes in resting-state EEG spectral activity;performance changes across 11 neuropsychological tests;APOE genotype distribution;circulating inflammatory and stress biomarkers (IL-6, TNF-*α*, high-sensitivity C-reactive protein, and cortisol);gut microbiota diversity (Shannon index);gut microbiota taxonomic composition; andfecal metabolomic profiles related to the gut–brain axis.

Detailed methodologies for each outcome measure are described in the following sections.

#### Clinical evaluations and laboratory testing

2.5.1

A structured research questionnaire will be administered to collect comprehensive baseline information, including age, biological sex, years of education, comorbidities, medication history, family history of neurodegenerative diseases, smoking and betel nut use, dietary preferences, eating habits, coffee or tea consumption (Zhang et al., 2026), bowel movement patterns, and prior experience with memorization training (e.g., structured memorization of Chinese Classics for more than 3 months). The questionnaire may be completed independently by participants or administered by trained research personnel. In addition to questionnaire-based assessments, participants will undergo basic physical examinations and detailed neurological evaluations.

#### Brain functional assessments

2.5.2

Electroencephalography (EEG) and non-contrast structural MRI will be performed prior to enrollment to exclude structural or vascular lesions that may account for cognitive decline, such as significant white matter hyperintensity (total Fazekas score ≥3; Fazekas et al., 1987) or internal carotid artery (ICA) occlusion. These exclusion criteria are informed by two lines of evidence. First, prior studies on cognitive reserve and white matter hyperintensities have demonstrated that increased white matter burden is associated with cognitive decline independent of Alzheimer’s disease pathology, potentially confounding the assessment of disease-specific effects (Lin et al., 2025). Second, ICA occlusion has been identified as a significant vascular risk factor for cognitive impairment and dementia (Baradaran et al., 2021). Therefore, excluding participants with substantial white matter hyperintensity or ICA occlusion helps minimize vascular contributions to cognitive decline and ensures a more homogeneous study population.

##### EEG acquisition and processing

2.5.2.1

Resting-state EEG recordings will be acquired using a standard 21-electrode montage positioned according to the international 10–20 system. Electrode impedance will be maintained below 10 kΩ, with a minimum sampling rate of 256 Hz. Recordings will be conducted in a quiet, dimly lit environment, with participants seated comfortably and instructed to remain awake with their eyes closed. EEG data preprocessing will be performed using Python 3 and the MNE-Python software package (Yu W. Y. et al., 2024). The preprocessing pipeline will include re-referencing, resampling to 250 Hz, and band-pass filtering between 0.1 and 41 Hz. Cleaned EEG signals will then be segmented into non-overlapping 2-s epochs for subsequent analysis.

##### MRI acquisition protocol

2.5.2.2

MRI data will be acquired using a 3.0 Tesla scanner (GE Signa Architect, Milwaukee, WI, USA) equipped with a 40-channel head coil. Both structural and functional imaging data will be collected. High-resolution three-dimensional T1-weighted images will be obtained using either spoiled gradient recalled echo (3D-SPGR) or inversion recovery-prepared SPGR sequences, with isotropic spatial resolution of 1 × 1 × 1 mm^3^. These images will be used for anatomical localization, co-registration, spatial normalization, and region-of-interest (ROI) definition. Functional MRI (fMRI) data will be acquired using T2-weighted echo-planar imaging sequences with whole-brain coverage. Imaging parameters will include: repetition time (TR) = 2000 ms, echo time (TE) = 35–60 ms (depending on optimization), flip angle = 90°, matrix size = 64 × 64, field of view ≈ 224 × 224 mm^2^, slice thickness = 4.0–4.4 mm with a 0.4 mm interslice gap, and voxel size ≈ 3.5–3.6 × 3.5–3.6 × 4.4 mm^3^. A total of 32 axial slices will be acquired in interleaved order.

##### Experimental paradigm and imaging schedule

2.5.2.3

Resting-state and task-based fMRI will be conducted at baseline and after the six-month intervention period. During resting-state scans, participants will be instructed to remain awake with their eyes closed and avoid structured cognitive activity. Task-based fMRI will employ a block-design paradigm. During task blocks, participants will be instructed to silently recite previously memorized Chinese Classics or mentally retrieve learned material, serving as the cognitive task. In addition, amyloid positron emission tomography (PET) imaging may be performed at participants’ own expense at any point during the study. Longitudinal follow-up PET imaging (e.g., 5 years post-intervention) will enable intra-individual comparisons of amyloid deposition trajectories and long-term disease progression.

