The study is designed as a randomized, assessor-blinded, controlled pilot study. A stratified block randomization sequence will be generated by an independent statistician using computer-generated random numbers, with stratification by age and sex to ensure balanced group allocation. Block sizes will be randomly varied to prevent predicting upcoming assignments. Allocation concealment will be ensured using the Sequentially Numbered, Opaque, Sealed Envelopes method; envelopes will be prepared and safeguarded by personnel not involved in recruitment, eligibility assessment, or intervention delivery. After eligibility assessment and informed consent are completed, a designated research assistant — otherwise uninvolved in outcome assessment — will open the envelope to reveal group assignment. Prior to allocation disclosure, all research personnel will remain blinded to the randomization sequence. Given that the intervention is behavioral in nature, complete blinding of participants and interventionists is not feasible. However, several measures will be implemented to minimize performance bias. Participants will be instructed not to discuss their group assignment with outcome assessors. Interventionists will have no role in outcome measurement or data analysis. Outcome assessors — including neuropsychological evaluators (psychologists) and radiologic technologists — will be formally blinded to group allocation throughout the trial and will be kept separate from the intervention team. To maintain blinding integrity, assessors will be reminded of their blinded status at each assessment visit, and any unblinding events will be documented and reported. Data analysts will similarly remain blinded to group assignment until the primary analysis is complete. The inherent risk of performance bias arising from participant awareness of group assignment will be mitigated by standardizing intervention protocols, using objective outcome measures where possible, and monitoring for differential dropout between groups.

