**Figure 1 fig1:**
[figure not shown]
Workflow of the randomized controlled trial. This flowchart illustrates the recruitment, screening, and enrollment process for participants. aMIC, abbreviated Memory Inventory for the Chinese; OPD, outpatient department; SCD, subjective cognitive decline.

The intervention group will undergo structured memorization training through recitation of Chinese Classics for 6 months. The intervention will be delivered by trained research assistants in weekly 60-min sessions, supplemented by approximately 10 min of individual daily practice over the six-month period. The control group will not receive memorization training during this period. To ensure reproducibility, a detailed intervention manual has been developed specifying recitation materials, progression criteria, and instructor guidance. All instructors will complete a standardized training program prior to the commencement of the study, encompassing both the theoretical rationale for the intervention and practical delivery skills. Instructor competency will be formally assessed before authorization to deliver sessions. As this study is conducted at a single center — China Medical University Hospital — inter-center standardization is not applicable to the current protocol; however, the intervention manual will be designed to support multi-site replication in future trials.

Intervention fidelity will be monitored through the following method. Daily home practice will be tracked via automated logs within the mobile application, capturing login frequency, session duration, and task completion rates. Adherence will be operationally defined as completion of at least 80% of the designated training, including at a minimum of 80% of scheduled training sessions and the fulfillment of at least 80% of the assigned daily practice throughout the six-month duration. Participants falling below this threshold at any monthly review will be contacted by the research team to identify and address barriers to engagement.

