Following completion of the initial six-month intervention phase, participants will be given the option to voluntarily continue recitation practice. The selection of a six-month intervention period is informed by the MEMO+ (Méthode d’Entrainement pour Mémoire Optimale) protocol developed by Sylvie Belleville and colleagues (Bier et al., 2015). Later studies from the same research team have demonstrated that participants receiving structured cognitive training exhibited significant improvements in memory recall performance, with effects persisting for at least 6 months post-intervention (Belleville et al., 2018). Furthermore, long-term follow-up over 5 years revealed that individuals who had undergone cognitive training experienced a slower decline in delayed memory performance and Montreal Cognitive Assessment (MoCA) scores compared with control groups (Belleville et al., 2024). These findings underscore the sustained benefits and potential long-term impact of continuous cognitive training.

Additional support for the selected intervention duration is derived from studies examining other forms of cognitively engaging activities. For example, interventions involving structured calligraphy practice have demonstrated that extending training duration over a six-month period leads to significant alterations in functional brain connectivity (Lee et al., 2024). Specifically, increased connectivity has been observed between the medial prefrontal cortex (mPFC) and right lateral temporal cortex (LTC), mPFC and right inferior parietal lobe (IPL), left hippocampal formation (HF) and right LTC, as well as between the left HF and right IPL (Lee et al., 2024). These findings suggest that prolonged engagement (6 months) in cognitively demanding tasks may induce measurable neuro-modulatory effects at the network level.

Taken together, a 6-month intervention period represents a balanced design choice: it is sufficiently long to allow for detectable behavioral and neurobiological changes, yet not so prolonged as to compromise participant adherence. Accordingly, outcome assessments will be conducted at baseline (time of recruitment), immediately after the six-month intervention, and at one-year and two-year follow-ups, with annual assessments thereafter until participants are no longer able to complete evaluations. The study will be conducted at China Medical University Hospital, primarily within the outpatient clinics of the Departments of Neurology or Psychiatry.

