The anticipated secondary outcome is intervention-induced change in task-based fMRI activation within bilateral fronto-striatal regions during active recitation of Chinese classics from T0 to T1. The fronto-striatal network — encompassing the dorsolateral prefrontal cortex, anterior cingulate cortex, caudate nucleus, and putamen — supports executive control, phonological working memory, and procedural learning, all of which are recruited during complex verbal recitation tasks (Ranjan and Singh, 2025). A training-induced decrease in fronto-striatal activation during recitation is the anticipated direction of effect, interpreted as increased neural efficiency: as recitation becomes more automatized through practice, the same cognitive output is achieved with lower metabolic demand, analogous to skill-learning-related neural efficiency observed in other trained cognitive domains (Kelly and Garavan, 2005).

EEG parameters and gut microbiota/metabolomic composition are designated as exploratory outcomes. Given that the study population comprises individuals with SCD, rather than overt neurodegenerative disease, significant alterations in EEG parameters may not be observed. EEG is included as an exploratory measure to characterize the electrophysiological signature of the SCD sample at baseline, and to detect any subclinical signal changes that may warrant inclusion as a sensitive biomarker in a future confirmatory trial. For the microbiota profile, the recitation training group is expected to show increased gut microbial alpha-diversity and enrichment of beneficial genera, including *Prevotella*, *Faecalibacterium*, and *Megamonas* (Sun Y. et al., 2023), as well as increased abundance of short-chain fatty acid-producing taxa, such as *Ruminococcus*, *Roseburia*, *Subdoligranulum*, and *Bifidobacterium* (Swarup et al., 2025), compared to controls. Results will be reported descriptively, including individual-level variability data, and effect sizes with 95% confidence intervals will be provided to inform the design of a future confirmatory trial.

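### The recitation task used for the secondary fMRI outcome relies on memorised material that the trial gives only to the intervention arm and only after baseline, so its change cannot be read as neural efficiency

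*Protocol article*

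**What the plan says.** Section 2.5.2.3 of the protocol article sets the schedule: "Resting-state and task-based fMRI will be conducted at baseline and after the six-month intervention period". It names a single block-design task, in which "participants will be instructed to silently recite previously memorized Chinese Classics or mentally retrieve learned material, serving as the cognitive task". The instruction is not split by arm or visit.

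Section 2.1 fixes who is trained and when. "The intervention group will undergo structured memorization training through recitation of Chinese Classics for 6 months", while "The control group will not receive memorization training during this period". On timing, "outcome assessments will be conducted at baseline (time of recruitment), immediately after the six-month intervention". The baseline scan therefore comes before any trial training.

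Section 3.3 gives the anticipated secondary outcome as intervention-induced "change in task-based fMRI activation within bilateral fronto-striatal regions during active recitation of Chinese classics from T0 to T1". It predicts a decrease and interprets it as neural efficiency, meaning that practice lets a person produce equal output at lower metabolic cost. Section 2.5.2.5 gives recitation against rest as an example of the first-level contrast and compares arms with directional two-sample t-tests.

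Section 2.5.1 collects "prior experience with memorization training (e.g., structured memorization of Chinese Classics for more than 3 months". That item is not among the exclusion criteria (2.2), the stratification factors (age and sex, 2.1) or the named covariates (age, sex, education and baseline cognition, 2.5.2.5).

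**The concern.** An efficiency reading needs the same task, done to the same standard, at both scans and in both arms. Here the trial itself changes what one arm has available to recite between the two scans. The arms may then differ at six months because one has a rehearsed text and the other is searching for something to retrieve, with no change in neural efficiency at all.

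The protocol's own rationale makes this more than a formality. The Introduction says that recitation activates motor and language cortex, and section 3.3 says that it recruits the fronto-striatal network. Whether a participant is really reciting should therefore affect the measured signal.

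The stake is the effect size carried forward. Sections 2.1 and 2.3 say that the pilot's estimates will inform the size of later definitive trials. Baseline scans cannot be repeated once training has begun.

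**Working it through.** **Side by side.** The table shows what the trial guarantees each participant to have available for the task.

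| | Baseline | Six months |
|---|---|---|
| Intervention | nothing from the trial; any prior memorisation | trained text, plus any prior memorisation |
| Control | nothing from the trial; any prior memorisation | nothing from the trial; any prior memorisation |

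Randomisation balances prior memorisation in expectation, so the two baseline cells are comparable with each other. The six-month cells are not, and the difference between them is created by the allocation. Within the intervention arm, baseline and six months also differ in content. Equal output is therefore not secured at baseline in either arm, or at six months in controls.

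**Illustration of size.** The documents give no figures for this, so every input below except the number per arm is an assumption.

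- *A*: difference in task activation between a participant with a memorised text and one without, in SDs of change.
- *p*: share with a text at baseline, equal in both arms.
- *f_I*, *f_C*: shares with a text at six months in the intervention and control arms.
- True plasticity: zero.
- 30 per arm (section 2.3); one regional summary per participant; one-sided 0.05.

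The expected change is A(f_I − p) in the intervention arm and A(f_C − p) in controls. The between-arm difference in change is A(f_I − p) − A(f_C − p) = A(f_I − f_C). It vanishes only if f_I = f_C or A = 0.

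| \|A\| | f_I | f_C | Size of artefact (SD) |
|---|---|---|---|
| 0.5 | 0.8 | 0.5 | 0.5 × 0.3 = 0.15 |
| 0.5 | 1.0 | 0 | 0.5 × 1.0 = 0.50 |
| 1.0 | 0.8 | 0.5 | 1.0 × 0.3 = 0.30 |
| 1.0 | 1.0 | 0 | 1.0 × 1.0 = 1.00 |

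**Direction.** Section 3.3 predicts a decrease, so the test of interest is in that direction. Power comes from the noncentral t distribution with 58 degrees of freedom.

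- If A is positive (having a text raises activation), the artefact pushes upwards. The chance of declaring a decrease falls from the nominal 0.05 to 0.013 at 0.15 SD and to below 0.001 at 0.5 SD or more. A real decrease of 0.5 SD would be cancelled by an artefact of the same size: −0.5 + 0.5 = 0.
- If A is negative (effortful search without a text activates more than fluent recitation), the artefact pushes downwards. A decrease would be declared with probability 0.14 at 0.15 SD and 0.985 at 1.0 SD, with no plasticity present.

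The documents do not settle the sign of A.

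**The plan's own figure.** The only calculated sample size is 383 per group (d = 0.18, one-tailed 0.05, power 0.80). It reproduces: exact power is 0.7997 at 382 and 0.8006 at 383. It was derived for neuropsychological scores and is no input here. It gives only a yardstick: most of the illustrated artefacts exceed 0.18 SD.

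**The case against.** The strongest reply is that the task can be done without trial training. The instruction allows retrieval of learned material in general, prior memorisation is recorded, and section 3.2 describes this kind of recitation as deeply rooted in local culture and schooling. Older participants may well know texts at baseline. This stands against one tempting inference, that task content is completely confounded with arm and visit: the documents do not show that controls cannot do the task. It does not restore comparability. Undefined material may differ by person, arm and visit, and the trained text is still added in one arm only.

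A second reply is that the endpoint deliberately targets automatisation of a practised skill, and that a common task would ask about transfer instead. That is a fair choice of question. But automatisation can be inferred only if output is equal at both scans.

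A third is that a journal article leaves task scripts to the full protocol. That would cover a missing detail. Here the stated task, schedule, control condition and interpretation do not fit together.

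Other stronger readings that a reader might infer are not supported:

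- *The technologist is unblinded by the task.* The article gives one instruction for all, the task is silent, and assessors "will be formally blinded to group allocation throughout the trial and will be kept separate from the intervention team". Unblinding would be a risk only if instructions came to differ by arm.
- *Silent recitation in 2.5.2.3 contradicts active recitation in 3.3.* Active can simply mean task as opposed to rest.
- *No performance is measured.* Section 2.4 has a scored six-month recitation assessment in the intervention arm and app-recorded practice time. Only a check linked to the scan is not described, and an article may omit that.
- *Nothing common to both arms is scanned.* Resting-state fMRI is planned at both visits with no restriction by arm.

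**Conclusion.** The concern holds for the task-based outcome. As written, the between-arm change in fronto-striatal activation cannot separate training-related efficiency from differences in task content or in ability to perform the task. It does not follow that the contrast contains no plasticity, only that plasticity cannot be isolated from it.

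The size cannot be derived from the documents. The 0.15 to 1.0 SD range rests on the assumed values of A, f_I and f_C, and it shrinks to zero if controls hold comparable material at six months. Either sign is possible, so the bias could hide the predicted decrease or produce one.

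The reach is limited. The resting-state primary outcome in section 3.3 does not use this task. Feasibility and acceptability, the primary aim in the Introduction, are also untouched. Section 3.3 itself calls the secondary outcome supportive and hypothesis-generating. This is a should-fix, best done before the first baseline scan.

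**What to change.** In section 2.5.2.3, specify one task that both arms can perform at both visits. It could be a text that all participants already know, or a short passage outside the training material, learned to a set criterion by everyone before each scan, with a parallel version at six months. Use identical instructions for all, which also protects the technologist's blinding.

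In section 3.3, base the secondary contrast on that common task. Keep the trained text as a descriptive six-month block in the intervention arm.

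In section 2.5.2.5, add prior memorisation experience, which is already collected, as a covariate. This deals with chance imbalance and between-person variation. It does not by itself remove the difference that training creates at six months.

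If the trained-text contrast is kept as the endpoint, define what controls and baseline participants are to retrieve, and drop the neural-efficiency interpretation.

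The cost is a script change, a few minutes of preparation per scan, and less direct sensitivity to the trained material.
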